## Methods and analysis

### Study design

The PROSECCA study will improve prostate cancer treatment by utilising data within EHRs that is currently not used in preparation of radiotherapy treatment plans. This is possible because of the ability to link clinical intervention with International Classification of Diseases (ICD-10) codes and the relative ease with which mass longitudinal digitalised health records, including radiotherapy data, can be linked together in Scotland.^17^ The power of the Scottish digital healthcare infrastructure for answering population-based questions has been demonstrated in other large-scale health data research projects, although there has been limited work in cancer.^18 19^
Figures1  2 show the current approach used to plan and treat patients receiving radiotherapy and how the addition of information from a patient’s EHR will be used in the study.

**Figure 1 F1:**
[figure not shown]
Graphical illustration of a typical radiotherapy workflow in which a patient undergoes imaging, typically CT, MRI and Positron Emission Tomography (PET), specifically for radiotherapy purposes. A: In general, creation of a radiotherapy plan uses a limited amount of information from a patient’s EHR. B: Additionally, little or no account of a patient’s EHR is considered at follow-up after treatment to establish what factors in a patient’s complex healthcare record indicate that they may have had a poor response to treatment, or an increased risk of side effects (toxicity) from radiation. With this knowledge, it would be possible to identify these patients earlier and adapt their treatment accordingly.

**Figure 2 F2:**
[figure not shown]
Graphical illustration of the radiotherapy workflow showing the inclusion of healthcare data from HSC-PBPP/PHS as proposed in the PROSECCA study. C: Here the creation of a radiotherapy plan uses significant personal information from a patient’s EHR. In addition, it will include information obtained from population-level analysis on the influence that other healthcare factors, which are documented in HSC-PBPP/PHS healthcare records, have on treatment response. D: Here, significant attention will be paid to a patient’s EHR after treatment to establish, and understand more about, the factors indicating that they may have had a poor response to treatment, or an increased risk of side effects (toxicity) from radiation. For example, it will be possible to study the protective effect that medications such as statins or antihypertensive medications have and how they may reduce radiotherapy-related toxicity.

The study aims to include complete data sets from approximately 15 000 prostate patients who received radiotherapy at one of the five Scottish cancer centres, namely Aberdeen, Dundee, Edinburgh, Inverness and Glasgow (Figure 3). This estimate was based on an initial assessment of data from NHS Scotland Information Services Division (ISD), which indicated that over the proposed timeframe approximately 25 000 patients with prostate cancer were treated with radiotherapy in Scotland. It has been assumed that 40% of data will be incomplete or not suitable for the endpoints, Prostate Specific Antigen (PSA) relapse-free survival and overall survival, and that 60% of data will be incomplete or not suitable for the endpoint radiotherapy toxicity reported from all sources. From this, for each of the three key endpoints, the expected number of significant events in the study population was estimated to be: PSA relapse-free survival=1125; overall survival=2175; radiotherapy toxicity=1200. These preliminary estimates indicate that even with this level of incomplete data, there is still a sufficient number of complete data sets available to achieve the project goals. More details on how these figures were obtained are included in table 1.

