#### Ensemble approaches/classical machine learning models

It is anticipated that the final classification will benefit from an ensemble approach using different AI/ML models to optimise classification. For example, decision trees, support vector machines, nearest neighbour and naive Bayes’ classifiers, all of which have been used extensively in previous radiotherapy and cancer classification problems.^25^,^31^

Serving as input data to these models will be unique information, or features, extracted from radiotherapy, imaging and EHR data. Currently, it is estimated that there will be, per time point of interest, more than 500 features of interest comprising:

Radiotherapy planning features (n=20+ features).Including, but not limited to, dose to prostate and organs at risk, organ volume, number of fractions, delivery technique, dose calculation algorithm.Image analysis/radiomic features (n=150+ features).Including texture/radiomics analysis based on low-level and high-level feature analysis, features based on organ shape and position, features derived from other approaches such as Fourier analysis and wavelet analysis.Clinical/patient-specific features from EHRs (n=431 features at multiple timepoints).Including PSA, staging, Gleason score, age, smoking history, comorbidities including prescription medications via ICD-10 indicative of diseases such as cardiovascular and diabetes.

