### Protocol

#### Patient selection

Patients with prostate cancer who have received external beam radiotherapy with radical intent are eligible for inclusion in the PROSECCA study. Patients must have had PSA recorded at regular intervals after radiotherapy, a radiotherapy planning CT and corresponding radiotherapy and healthcare data available.

Patients who have received external beam radiotherapy as part of a palliative treatment schedule are not eligible for inclusion in the study, as well as those with no PSA information and follow-up healthcare and imaging data.

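### Entry to the cohort depends on complete data and on PSA and follow-up records made after radiotherapy, which can bias predicted risks and needlessly removes men from overall survival

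*Protocol article*

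**What the plan says.** Study design gives the aim: "The study aims to include complete data sets from approximately" 15 000 men. The source is about 25 000 men, described only by the fact that "patients with prostate cancer were treated with radiotherapy in Scotland" over the study period; treatment intent is not given.

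Two loss assumptions follow. The first is that "It has been assumed that 40% of data will be incomplete or not suitable for the endpoints" of PSA relapse-free survival and overall survival. The second is that "60% of data will be incomplete or not suitable for the endpoint radiotherapy toxicity reported from all sources". The section judges adequacy by the number left, concluding that "there is still a sufficient number of complete data sets available to achieve the project goals".

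Patient selection turns availability of records into eligibility: "Patients must have had PSA recorded at regular intervals after radiotherapy, a radiotherapy planning CT and corresponding radiotherapy and healthcare data available". Besides palliative treatment, it excludes further men on records: "as well as those with no PSA information and follow-up healthcare and imaging data".

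Table 1 reduces the 15 000 again, to 11 250 for the 5-year PSA endpoint and 7500 for 10-year overall survival. It uses 10 000 for 5-year toxicity. Table 2 lists the national deaths data among the linked datasets. The objectives say that predictions will be available before treatment as well as during it.

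**The concern.** A planning CT and radical intent are known when radiotherapy starts. A regular PSA series and follow-up healthcare data are not, because they come into being afterwards. A man who dies early, moves away or rarely attends is less likely to have them. Selecting on them can tie entry to the outcomes being predicted: relapse, survival and toxicity.

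Two consequences follow. First, the models are developed in men who turned out to be well recorded but applied before treatment, when nobody knows who those men will be. Absolute risks, predictor effects and calibration can all be affected. Second, for overall survival the PSA condition gives up information already held, since death can be ascertained from the linked national records whether or not PSA was measured.

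These are entry conditions. An analysis plan written later cannot recover men whom eligibility has already removed.

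**Working it through.** **1. Reproduce the article's counts** (Study design and Table 1; events = men retained × event rate).

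- Complete data sets: 25 000 × (1 − 0.40) = 15 000. Matches.
- PSA relapse: 15 000 × 0.75 × 0.10 = 11 250 × 0.10 = 1125. Matches, if Table 1's 75% attrition is read as 75% retained.
- Overall survival: 15 000 × 0.50 × 0.29 = 7500 × 0.29 = 2175. Matches.
- Toxicity: 25 000 × (1 − 0.60) × 0.12 = 10 000 × 0.12 = 1200. Matches, if the printed 60% of 25 000 is read as 40% retained.

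**2. Precision cost.** Standard errors scale roughly as 1/√N, so the inflation factor is √(N eligible ÷ N kept). The split of the loss between ineligible and incomplete men is not given, so the full range is shown.

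| Share of the loss that is true ineligibility (assumption) | PSA and survival, 15 000 kept | Toxicity, 10 000 kept |
|---|---|---|
| None | √(25 000/15 000) = 1.29 | √(25 000/10 000) = 1.58 |
| Half | √(20 000/15 000) = 1.15 | √(17 500/10 000) = 1.32 |
| All | 1.00 | 1.00 |

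In the first row, events would be at most 25 000 × 0.75 × 0.10 = 1875 (PSA), 25 000 × 0.50 × 0.29 = 3625 (survival) and 25 000 × 0.12 = 3000 (toxicity). With half the loss ineligible they would be 1500, 2900 and 2100. Table 1's further cuts to 75% and 50% are left in place here, since they may reflect limited follow-up.

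**3. Illustration of selection bias.** Let p be the true event rate and r the probability of being retained for men with the event, relative to men without it. The observed rate is p·r ÷ (p·r + 1 − p). The values of r are assumptions; the document gives none.

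- 10-year mortality, p = 0.29: r = 0.7 gives 0.203/0.913 = 22.2%; r = 0.9 gives 0.261/0.971 = 26.9%.
- Toxicity, p = 0.12: r = 0.8 gives 0.096/0.976 = 9.8%; r = 1.25 gives 0.150/1.030 = 14.6%; r = 1.5 gives 0.180/1.060 = 17.0%.

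For mortality, r below 1 is the natural direction, because early death cuts the PSA series short. For toxicity either direction is possible: men with symptoms may be seen and recorded more, or be lost sooner.

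**4. The survival endpoint set against the data sources.** Study design applies the same 40% loss to overall survival as to PSA relapse. Patient selection applies the PSA condition to every man, whatever the endpoint. Table 2 nevertheless includes national deaths data, and Study design says the Community Health Index number identifies every healthcare episode in Scotland. Ascertaining death does not require PSA.

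**The case against.** The Study design text is feasibility counting. It states an aim, assumptions and preliminary estimates, and a condensed article may leave the handling of missing values to an analysis plan. That stands, and it limits the point in four ways.

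- A reader might infer that 40% to 60% of eligible men are thrown away as incomplete. The document does not say so. Its percentages combine incomplete with unsuitable data, and palliative cases, which may be among the 25 000, are properly excluded. The share lost to incompleteness is unknown.
- A reader might infer a complete-case analysis of predictors. No section says that a man with a missing predictor is dropped from a model.
- A reader might combine the target of complete data sets with the planned "more than 500 features of interest comprising" the radiotherapy, imaging and health-record groups, and infer that no feature may be missing. Patient selection asks for completeness by component (PSA, planning CT, radiotherapy and healthcare data), and sources such as the stroke audit or renal registry are naturally empty for most men.
- Table 1's halving for overall survival may reflect 10-year follow-up in men treated from 2010 to 2022. It need not mean that men were dropped for missing PSA.

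The planned validation in Hamlet-RT does include calibration, but it would not by itself rule out selection in the development cohort. None of these arguments answers the Patient selection rule, which is stated as eligibility and looks at records made after treatment.

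**Conclusion.** The point holds as a criticism of a stated inclusion rule. The study population is built on complete data sets, and entry requires records that arise only after radiotherapy, so men are selected on something that can depend on the outcomes. For overall survival the PSA condition is also unnecessary, given the linked death records.

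The precision cost ranges from none, if the whole loss is ineligibility, to standard errors 1.29 times (40% loss) or 1.58 times (60% loss) larger. The upper ends assume that every excluded man is eligible and fully recoverable, which cannot be so for men with no PSA or toxicity outcome. Bias is the larger worry. Its direction and size cannot be derived from the document, and the illustrated shifts rest on assumed retention ratios. It does not follow that calibration will fail, only that the rule puts it at risk. This should be changed before models are fitted.

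**What to change.** 1. Define the cohort by what is known at the start of radiotherapy: external beam treatment with radical intent and planning data available.
2. Report the path from 25 000 men with separate counts for not eligible and for incomplete, by endpoint.
3. Require PSA availability only for the PSA endpoint.
4. Keep every eligible linked man in each endpoint for which his outcome is observed or censored. Treat short follow-up as censoring.
5. Handle missing predictors inside each training fold, by multiple imputation or by learners that accept missing values.
6. Compare included with excluded men by centre, year, age and stage, and report the complete-data cohort as a sensitivity analysis.

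The cost is more computation and an extra comparison table; no new patient contact is needed. The drawback is that imputation rests on a missing-at-random assumption, which the sensitivity analysis can probe but not prove.

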**Figure 3 F3:**
[figure not shown]
Map showing the location of the five Scottish Cancer Centres and in brackets the number of clinical linear accelerators at each location.

**Table 1 T1:** Preliminary estimates of the number of events for the three main endpoints of interest, PSA relapse-free survival, overall survival and radiotherapy toxicity as defined from all sources.

Endpoint of interest	Approach used to estimate events	Events
PSA relapse-free survival	5-year endpoint, 10% event rate based on the trial, a randomised phase III multi-centre trial of Conventional or Hypofractionated High dose Intensity modulated radiotherapy for Prostate cancer, (CHHiP) ^46^ Sample size of 11 250 based on 75% attrition in this data (75% of 15 000)	1125
Overall survival	10-year endpoint, 29% event rate based the trial, a Randomised controlled Trial of high dose versus standard dose conformal radiotherapy for localised prostate cancer, (RT01)^11 46 49^ Sample size of 7500 based on 50% attrition in this data (50% of 15 000)	2175
Radiotherapy toxicity (all sources)	5-year endpoint, 12% event rate for ≥ grade 2 based on CHIIP trial high grade group^11 46 49^ Sample size of 10 000 based on much higher attrition of 60% attrition for this endpoint of interest (60% of 25 000=10 000 followed by 12% of 10 000)	1200

Estimates were based on data from NHS ISD, Scotland, Prostate Cancer Incidence.

PSA, prostate specific antigen.

Each of the five Scottish cancer centres involved in the study uses the same commercial database for storing information on patients receiving radiotherapy for prostate cancer. This database, known as ARIA, is supplied by Varian Medical Systems^20^ and is used to maintain a complete independent record of a patient’s treatment, which is required by law under the Ionising Radiation (Medical Exposure) Regulations 2017 .^21^ Separately, Public Health Scotland (PHS), Scotland’s national public health body, holds health and social care data for the entire Scottish population (5.4 million) as far back as the 1970s. Since this time, every NHS patient treated in Scotland has been allocated a unique identifier at birth, or on registering with Scottish healthcare services. This 10-digit numeric code, known as the Community Health Index number (CHI), is the primary mechanism for patient identification for every healthcare episode that happens in Scotland, making it straightforward to access and find information about an individual patient.

All healthcare records held by PHS are held within national datasets, which adhere to international standard coding definitions.^22^ Access to information held within a specific national dataset for research can be made through the Electronic Data Research and Innovation Service (eDRIS) team. The eDRIS team serves as the PHS point of entry for all projects, such as PROSECCA, that wish to use national datasets for research purposes. Central to the PROSECCA application to PHS was the identification of the national datasets of interest and the specific variables within these datasets that would be meaningful in assessing radiotherapy response. The list of national datasets held by PHS that will be accessed in the PROSECCA study, and linked to radiotherapy-specific information, is shown in table 2. Online supplemental table 4 also includes a brief justification for the use of each dataset, a requirement of the access request, and where available a recent scientific reference indicating the association with prostate cancer. Figure 4 illustrates how the data from the ARIA radiotherapy system and the data from the list of national datasets will be combined into a multidimensional array for further processing.

**Table 2 T2:** Complete list of the national datasets held by PHS, and the number of variables within each, that will be accessed in the study.

National data set		Description	Number of unique features (n=431)
No.	Abbr. name		
1	SMR 00	Scottish Morbidity Record outpatient attendance	33
2	SMR 01	SMR general/acute inpatient and day case attendance	21
3	SMR 06	SMR Scottish Cancer Registry—The Scottish Cancer Registry and Intelligence Service has developed a national cancer intelligence platform that serves as a single point of entry to national cancer-specific data. The registry holds over 1 800 000 records dating back to 1958 when the registry began as well as data from the three cancer screening programmes in Scotland (bowel, breast and cervical)	107
4	GP Data	Coded GP-specific events that may be related to postradiation toxicity (eg, rectal haemorrhage, urinary infection and proctitis)	12
5	GP OOH	Coded GP out of hours—primary care out of hours data where specific events that may be related to post-radiation toxicity may be recorded (eg, rectal haemorrhage, urinary infection and proctitis)	24
6	NRS Deaths	National Records of Scotland deaths data	14
7	A&E2	Accident & Emergency	47
8	PIS	Prescribing Information Systems	16
9	SSCA	Scottish Stroke Audit	33
10	SBoSP	Scottish Bowel Screening Programme	25
11	SRR	Scottish Renal Registry	17
12	SHFA	Scottish Hip Fracture Audit	17
13	PDS	Dementia postdiagnostic support	10
14	DAISy	Drug and Alcohol Information System	12
15	SDMD, SMR25a, SMR25b	The Scottish Drug Misuse Database	11
16	WT	Waiting Times	7
17	SCS	Smoking Cessation Services	14
18	MS	Multiple Sclerosis	6
19	TRAK	Healthcare Information System	2
20	SPIDER	Streptococcus Pneumonia surveillance	3

**Figure 4 F4:**
[figure not shown]
Detailed methodology of the PROSECCA study showing, from left to right, data entry into the platform from the ARIA radiotherapy information system and various healthcare data sets from PHS. All data processing will be carried out within the secure environment described in figure 5. CNN, Convolutional Neural Network; IM, Imaging; LASSO, least absolute shrinkage and selection operator; RNN, Recurrent Neural Network; TNM, Tumour, Node, Metastasis.

### Study objectives

The primary objectives of the PROSECCA study are to use advanced artificial intelligence and machine learning (AI/ML) techniques to analyse the EHRs of patients with prostate cancer who underwent radiotherapy in the treatment of their cancer and to establish what factors indicate that a patient may have a poor response to treatment, or an increased risk of side effects from their treatment. The secondary objectives are to use these factors to build predictive models that identify these patients much earlier than is currently possible.

Figure 4 summarises the methodological approach of PROSECCA and the key parameters/features that will be used as input to different AI/ML models. With such an extensive dataset, the majority of which has not been analysed in any way, the preliminary phase of the study will use AI/ML frameworks already proven to work well in other big-data applications (eg, multimodal deep learning models, pretrained deep learning models and ensemble approaches). These will be adjusted to estimate biochemical relapse-free survival, overall survival and risk of toxicity from these data. Specifically, this will be approached by developing a number of ML models.

#### Multimodality deep learning models

Efficiently combining multimodality data within deep learning frameworks is challenging. The planned initial approach will involve building convolutional neural networks (CNNs) and vision transformers for imaging data and using other approaches for radiotherapy and clinical features, such as recurrent neural networks (RNNs).^23^ The output from these will be concatenated and passed to densely connected layers for classification. Labelled data will be available from: radiotherapy planning, medical imaging and EHR information (figure 4).

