**Methods and analysis:**

The PROSECCA study is a large multidisciplinary project, the purpose of which is to analyse healthcare records from up to 15 000 patients with prostate cancer who underwent radiotherapy in the treatment of their cancer in Scotland between 2010 and 2022. Through the linkage of data obtained specifically for radiotherapy and data held within each patient’s unique electronic health record (EHR), the factors that indicate why some patients have a poor response to treatment, or an increased risk of side effects from radiation, will be identified. This will be made possible by the use of artificial intelligence and machine learning (AL/ML), which will help to identify at-risk patients earlier and allow adaptation of their treatment accordingly.

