### Prediction of a patient’s risk of radiation toxicity and tumour control

Using the linked dataset, predictive factors will be established indicating that a patient may have a poor response to treatment, including the increased risk of normal tissue toxicity. This information will be available both (1) prior to treatment and (2) during the course of treatment.Medium (5 year) and long (10 year) estimates of three clinically significant endpoints: (1) PSA relapse-free survival, (2) overall survival and (3) radiotherapy toxicity.To ensure maximum clinical impact, a software application, available to clinicians in the clinic, will be developed to use these predictive factors to identify (1) the most appropriate form of therapy, (2) the most appropriate dose and fractionation schedule and (3) the optimal time and how best to adapt treatment.To establish a pathway and methodology showing how the approach developed in PROSECCA can be applied to other tumour sites (eg, lung and head and neck cancer), thereby benefiting a much larger number of patients treated with radiotherapy.

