#### Outcome measures

The primary outcome measures of the PROSECCA study are to establish what a patient’s probability of relapse-free survival, metastatic-free survival, cause-specific and overall survival will be when data from their EHR is combined with radiotherapy-specific parameters.

Secondary outcome measures include imaging-derived biomarkers and the independent and codependent predictive power of variables held within each patient’s EHR (online supplemental table 4) for prediction of primary outcomes.

Research and technical-scientific secondary outcomes include the curation of a population-based radiotherapy database containing imaging, dose and radiotherapy planning data and linked healthcare data from the national PHS archive. This also includes the establishment of a secure virtual environment, with high-performance computing capability, for rapid model development and outputs on the performance of a range of AI/ML models in predicting primary outcomes. Once established, this resource will also be used for future discovery research as well as validation of findings made by other researchers.

Patient-specific secondary outcomes will be in the form of a testbed for investigating the relationship between biochemical failure and radiotherapy-specific parameters such as dose, fractionation and planning techniques. This will also include how to personalise, or adapt, a patient’s course of radiotherapy by suggesting: the best form of therapy; the most appropriate dose and fractionation schedule; the optimal time to adapt; and the best mechanism for assessing any proposed personalised treatment. This will be available through an easy-to-use app.

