Accessing the data required for PROSECCA, which is generally stored in different databases and formats across organisations, is not only technically difficult but must align with the data protection laws on data minimisation as defined in Article 5 of the UK GDPR .^39^ Adherence to these standards is a requirement for access to health data in Scotland and through delegated authority from the NHS Scotland Chief Executive Officers and the Registrar General of National Records of Scotland these standards are upheld by HSC-PBPP. The purpose of the HSC-PBPP panel is to scrutinise requests for access to health data by researchers, organisations or individuals, and to act as the final arbiter in deciding whether it is appropriate for the request to be granted in full or in part. In this capacity, HSC-PBPP is not an ethical review body, and there is an expectation that requests have received favourable ethical reviews from an ethics panel before submission. While the panel works hard to strike a balance between safeguarding the privacy of those whose data are being released and making the best possible use of health and social care data for the benefit of the population, the sheer number of variables and datasets requested, combined with the complexity of the PROSECCA study, meant that this took a considerable amount of time. With initial discussions beginning in October 2022 and first access to linked health data in February 2025, all parties are aware that a more simplified and streamlined process for accessing public data would have societal and scientific benefits. Research Data Scotland (RDS), a not-for-profit charitable organisation, was set up in 2023 to address these issues and make it faster and simpler for researchers to access public sector data for research.^48^ The PROSECCA study has been used as a case study by the RDS team to demonstrate where this new approach to access may have been helpful.

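### The article names only classifiers for survival outcomes at 5 and 10 years, yet at the one linkage date it gives only about 39–43% of men could have 10 years of follow-up

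*Protocol article*

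**What the plan says.** The targets are time-to-event outcomes. Outcome measures (Protocol article) lists as primary a patient's "probability of relapse-free survival, metastatic-free survival, cause-specific and overall survival". The objectives under Prediction of a patient's risk of radiation toxicity and tumour control promise "Medium (5 year) and long (10 year) estimates of three clinically significant endpoints": PSA relapse-free survival, overall survival and toxicity.

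The named methods are classifiers. For the deep networks, Multimodality deep learning models says: "The output from these will be concatenated and passed to densely connected layers for classification". The section on ensembles and classical models speaks of a final classification and gives as examples "decision trees, support vector machines, nearest neighbour and naive" Bayes. Study objectives says that existing frameworks will be adjusted so as to estimate relapse-free survival, overall survival and toxicity risk. It then leads straight into those model descriptions without saying what the adjustment is.

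On timing, the cohort is men "who underwent radiotherapy in the treatment of their cancer in Scotland between 2010 and 2022", and the Discussion gives "first access to linked health data in February 2025". No data cut-off for analysis is stated.

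On numbers, Study design says "The study aims to include complete data sets from approximately 15 000 prostate patients". Table 1 then counts events as a fixed-horizon proportion of a reduced sample: 11 250 men at 5 years for PSA relapse, and 7500 at 10 years for overall survival, the latter "based on 50% attrition in this data".

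**The concern.** A man treated after early 2015 and alive in February 2025 has no 10-year status. A plain classifier must call him event-free, leave him out, or restrict training to an earlier cohort. The first understates risk. The second overstates it if early deaths among recent patients are kept while their surviving contemporaries are removed. The third avoids both biases but gives up most of the cohort, including the men treated most recently.

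The first choice also distorts the search for predictive factors, which is the primary objective. Number of fractions and delivery technique are among the planned features, and the Introduction describes hypofractionation as more recent. Under an event-free label, anything introduced late would look protective simply because follow-up on it is short. The predictions are meant to feed a decision tool for clinicians, so the calibration of the absolute probabilities matters.

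**Working it through.** **Table 1 reproduced.** Events = sample × event rate: 11 250 × 0.10 = 1125; 7500 × 0.29 = 2175; 10 000 × 0.12 = 1200. All three agree with the table. The 5-year PSA sample is 75% of 15 000 kept, although the table words it as 75% attrition.

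**Inputs from the article.** Treatment 2010–2022; first linked access February 2025 (2025.12); 15 000 men; 29% deaths at 10 years; 10% PSA relapse at 5 years.

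**Assumptions.** Data cut at 2025.12; uniform accrual from the start of 2010 to the end of 2022 (W = 13 years, shortest follow-up m = 2.12 years) or to the start of 2022 (W = 12, m = 3.12); constant hazard; administrative censoring only.

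**Share with H years of potential follow-up** = (2025.12 − H − 2010)/W.
- H = 10: 5.12/13 = 39.4%; 5.12/12 = 42.7%. That is 5908 to 6400 of 15 000 men, with 57–61% lacking 10 years.
- H = 5: 10.12/13 = 77.8%; 10.12/12 = 84.3%. So 16–22% lack 5 years.
- If accrual rose or fell by 3–5% a year (13-year window), the 10-year share runs from 32% to 47%.
- The 10-year share reaches half at a cut of 2010 + 10 + W/2, which is January 2026 (W = 12) or July 2026 (W = 13). At January 2027 it is 54–58%.

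**10-year mortality under three labelling rules.** λ = −ln(0.71)/10 = 0.03425 per year. Deaths observed among men with less than 10 years of potential follow-up, as a share of the cohort, are D = [(10 − m) − (e^(−λm) − 0.71)/λ]/W.
- W = 13: D = (7.88 − 6.42)/13 = 0.112. W = 12: D = (6.88 − 5.51)/12 = 0.114.
- Censored men called event-free: D + share × 0.29 = 0.112 + 0.114 = 22.6%; 0.114 + 0.124 = 23.8%.
- Known status only: 0.226/(0.112 + 0.394) = 44.7%; 0.238/(0.114 + 0.427) = 44.0%.
- Only men with 10 years of potential follow-up: 29%, unbiased under these assumptions, with 15 000 × 0.394 × 0.29 = 1713 to 15 000 × 0.427 × 0.29 = 1856 deaths.

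**5-year relapse, true value 10%.** The same formulas with λ = −ln(0.90)/5 = 0.02107 give 9.4–9.7% (censored called event-free) and 11.4–11.8% (known status only).

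**Apparent protection from recent treatment.** Under the event-free label, a man with the shortest follow-up carries a death label with probability 1 − e^(−λm) = 7% (m = 2.12) or 10% (m = 3.12), against 29% for a man treated in 2010 with the same hazard.

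**The case against.** The strongest reply is that the article does not fix the analysis this tightly. Study objectives allows for adaptation to survival estimation and calls this a preliminary phase; the deep-learning approach is described as initial, and the classical models are offered as examples. The caption to Figure 4 lists LASSO, which the text never describes, so the visible list may be incomplete. How censored men are labelled could sit in the full protocol or analysis plan. This stands as a reason for not calling the bias established. It does not remove the point: the promised adjustment leads directly into classifiers, and classification is the stated output.

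Some stronger readings are tempting, but the article does not support them.
- A reader might infer that the plan discards over half the cohort. Table 1 keeps exactly half at 10 years and three quarters at 5. The larger loss depends on an assumed February 2025 cut, and that date is only the first access.
- A reader might infer that Table 1 drops censored men. Its samples are consistent with fixed-horizon complete cases, but it gives preliminary event counts, not an analysis set, and does not say why the men are lost.
- Using all 15 000 men would give about 3395 to 3571 deaths within 10 years, 56–64% above 2175. That comparison is not like-for-like, because it applies no attrition to one side and 50% to the other. Some of that attrition may be missing data.
- A yes/no label can represent a competing death: relapse by 5 years, with earlier death coded as no, targets cumulative incidence. Scores from support vector machines or naive Bayes can be recalibrated, and External validation commits to checking calibration and to TRIPOD reporting.

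**Conclusion.** The point holds in a limited form. The article names classifiers for censored outcomes and no method that handles censoring. At 10 years the simple labelling rules either bias mortality substantially (about 23–24% or 44–45% against 29%) or cost 57–61% of the men. At 5 years the bias is within about two percentage points, or 16–22% of men are lost.

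The sizes rest on a February 2025 cut, uniform accrual, a constant hazard and administrative censoring only. A cut after about mid-2026 would give most men 10 years of potential follow-up, but 42–46% would still lack it at January 2027. Whether any bias occurs depends on a labelling rule that the article does not state. This is a cheap improvement, below must-fix.

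**What to change.** - State a data cut-off date.
- For the 10-year endpoints at least, and preferably for all, replace plain classification with time-to-event learning that uses each man up to his censoring date. Examples are penalised Cox regression, random survival forests, or a Cox-loss or discrete-time output layer on the deep networks. Where a classifier is retained, weight it by the inverse probability of censoring.
- Say explicitly how death is handled as a competing event for PSA relapse and toxicity, and death from other causes for cause-specific survival.
- Evaluate the 5- and 10-year predictions by calibration, censoring-adjusted discrimination and a censoring-adjusted Brier score.

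The cost is a changed loss function and evaluation code. Some off-the-shelf classifiers would need weighting or would drop out of the ensemble. No new data are required.
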